## Abstract

Upper limb motor dysfunction after stroke is a serious threat to the living quality of patients and their families. Recovery of upper limb motor function after stroke largely relies on the activation and remodeling of neural circuits. rTMS (repetitive transcranial magnetic stimulation) has been proved to promote the reconstruction of neural synapses and neural circuits. However, there are still a large number of patients who cannot fully recover and leave behind varying degrees of dysfunction. Considering the systemic pathology after stroke, in addition to focal brain injury, stroke can also cause extensive dysfunction of peripheral organs. The rehabilitation strategy for stroke should combine the treatment of primary brain lesions with the intervention of secondary systemic damage. The aim of this trial is to verify the efficacy of rTMS synergize with Tui Na (Chinese Massage) on upper limb motor function after ischemic stroke, and to explore the mechanism of activation and remodeling of sensorimotor neural circuits with functional near-infrared spectroscopy. Ninety patients will be randomly assigned to either rTMS + Tui Na + conventional rehabilitation group (the experimental group) or rTMS + conventional rehabilitation group (the control group) in 1:1 ratio. Intervention is conducted five sessions a week, with a total of twenty sessions. The primary outcome is Fugl-Meyer Assessment, and the secondary outcomes include Muscle Strength, Modified Ashworth Assessment, Modified Barthel Index Assessment, motor evoked potentials and functional near-infrared spectroscopy. There are four time points for the evaluation, including baseline, 2 weeks and 4 weeks after the start of treatment, and 4 weeks after the end of treatment. This study is a randomized controlled trial. This study was approved by Institutional Ethics Committee of Shanghai Third Rehabilitation Hospital Affiliated to Shanghai University of Traditional Chinese Medicine (approval No. SH3RH-2021-EC-012) on December, 16th, 2021. The protocol was registered with Chinese Clinical Trial Registry (ChiCTR2200056266), on February 3th, 2022. Patient recruitment was initiated on February 10th, 2022, and the study will be continued until December 2023.

## Background

Epidemiological investigation shows that stroke seriously threatens safety and quality of life in the world (1). Ischemic stroke accounts for a higher proportion than that of hemorrhagic stroke. Most patients have motor dysfunction, especially upper limb (UL) motor dysfunction after stroke (2). UL movement is more delicate and complex, and its unsatisfactory recovery can reduce patients' activities of daily life and seriously affect the living quality of patients and their families (3). Therefore, UL motor dysfunction is a key and challenging point in rehabilitation after stroke.

Transcranial magnetic stimulation (TMS) is a neuromodulation technique for treating nervous and mental diseases in recent years. Repetitive transcranial magnetic stimulation (rTMS) is a continuous, repetitive mode of TMS, and it has been proved that rTMS has a good effect on neurological disorders. The latest guideline in 2019 recommended TMS as an A level for treating UL motor dysfunction in subacute stroke (4). Research has shown that rTMS can promote the regulation of microenvironmental factors, glial cell activity, and nerve fiber myelin sheath repair in the injured area, and promote the reconstruction of neural synapses and neural circuits (5–7). However, there are still a large number of patients who cannot fully recover and leave behind varying degrees of dysfunction (8). Therefore, while continuously improving the technology of rTMS, such as accuracy and treatment depth, it is necessary to find other methods to synergize with rTMS to enhance the therapeutic effect. Currently, there are some deficiencies in the combination between rTMS and other treatments (such as neuromuscular electrical stimulation, physical therapy and occupational therapy). The treatment mainly focuses on the brain and limbs, but does not pay attention to the influence of systemic pathology on the recovery of UL, and there is no good intervention method for systemic pathological injury (9).

Considering the systemic pathology after stroke, in addition to focal brain injury, stroke can also cause extensive dysfunction of peripheral organs. Stroke will profoundly change the autonomic nervous system, hypothalamus-pituitary-adrenal axis, immune system and fascia and muscle system, resulting in further systemic damage (10). In turn, systemic pathological changes after stroke promote the progress and prognosis of brain injury to a great extent. Especially in the elderly, it usually leads to more serious systemic damage and a worse prognosis after stroke (9). Before the stroke, the central and peripheral organ systems of a large number of elderly patients have been affected by varying degrees of structural and functional degradation because of continuous exposure to normal aging or chronic low-grade systemic inflammation and other pathological backgrounds. All of these “silent” pathology before stroke have laid the foundation for the emergence of systemic abnormalities caused by stroke (9). After the stroke, excitotoxicity, neuroinflammation, energy disturbance, oxidative stress, and other pathological processes work together, combined with previous complications, to cause or aggravate the structural changes and functional damage of multiple peripheral organs (11). Therefore, stroke should be regarded as a systemic disease with a profound impact on the surrounding organs. The rehabilitation strategy for stroke should combine the treatment of primary brain lesions with the intervention of secondary systemic damage.

Tui Na (Chinese massage therapy) is a relatively simple, inexpensive and non-invasive intervention, and has been used to treat stroke patients for many years in China. Tui Na mainly acts on specific parts of the body through manipulation, on the one hand, it plays a local therapeutic role in the body, on the other hand, it can also have a certain impact on various systems of the body through nerves, body fluids and other ways, so as to achieve the role of treating diseases (12). Clinical observation suggested that Tui Na might be a safe and effective treatment for post-stroke UL motor dysfunction (13, 14). Although the mechanism of Tui Na on treatment of post-stroke motor dysfunction is limited, some possible mechanism was proposed. Tui Na manipulation stretched the muscle–tendon complex and stimulate the Golgi tendon organ that could inhibit alpha motor neurons and reduce spasm (15). Tui Na manipulation might reinforce sensory stimulation and activate the gamma efferent fibers of muscle stretch receptors that make receptors more sensitive to stretch (15). Soreness and distension that was caused by Tui Na manipulation will excite the sensory cortex, thus inhibit reticular formation of brainstem and decrease the muscle tone (15). For more than two thousand years, traditional Chinese medicine therapists have been using Tui Na act on governor meridian-related acupoints to treat spinal-related diseases and many visceral disorders (16). The spine is the pillar of the human body and the medium that connects the brain and the peripheral organs. The spine is the pathway of the governor meridian in traditional Chinese medicine, which dominates people's life activities (17). The spine contains the spinal cord, with spinal nerves and sympathetic pathways on both sides. Although there are great differences in theory and technology between traditional Chinese and western medicine, they are almost the same in understanding the importance of the spine and preventing and treating diseases by adjusting the spine and its related surrounding tissues.

Based on the above research background, we adopt the strategy of rTMS to synergize with Tui Na to promote the recovery of UL motor dysfunction after ischemic stroke. fNIRS (functional near-infrared spectroscopy) will be used as a technique for sensorimotor cortex activity monitoring and brain plasticity evaluation. The function of Tui Na is reflected in two aspects:1. Tui Na will be used to stimulate the peripheral sensory nerve, promote the activation of the cortical sensorimotor network, and then activate the corticospinal tract with rTMS from the cortical motor area (M1) aimed at the reconstruction of “sensory afferent-cortical integration-motor execution,” in order to obtain the effect of synergy-enhancement. 2. The extensive effects of Tui Na on autonomic nerve, fascia and muscle system can promote the function of a wide range of peripheral organs, to promote the prognosis of stroke. Therefore, our primary objective was to identify a protocol for a randomized controlled trial to evaluate the effects of rTMS synergizing with Tui Na on the motor function of the UL in patients with ischemic stroke. We hypothesized that the treatment of rTMS synergized with Tui Na can promote the improvement of UL motor function after ischemic stroke and activate and remodel sensorimotor cortex activity.

## Methods/design

The study is a prospective, single-center, randomized, parallel-controlled design. Ninety patients will be randomly assigned to either rTMS + Tui Na + conventional rehabilitation group (the experimental group) or rTMS + conventional rehabilitation group (the control group) in 1:1 ratio. There are four time points to evaluate the efficacy, including baseline, 2 weeks and 4 weeks after the start of treatment, and 4 weeks after the end of treatment. Intervention will be conducted five sessions a week, with a total of twenty sessions (Figure 1). Each patient will be required to sign an informed consent form before participation. Patients will be informed of the purpose of the research, the procedures involved, the expected completion time, potential adverse reactions and possible benefits. The protocol is registered with Chinese Clinical Trial Registry (ChiCTR2200056266), registered on February 3^th^, 2022.

**Figure 1 F1:**
[figure not shown]
Summary of the study design.

### Eligibility criteria and recruitment

We will screen stroke patients who had treatment at Shanghai Third Rehabilitation Hospital Affiliated to Shanghai University of Traditional Chinese Medicine from February 2022 to December 2022 based on electronic medical records.

### Inclusion criteria

People will be eligible for inclusion if they meet the following criteria: (1) First ever unilateral ischemic stroke diagnosed by imaging and the course of the disease ranged from 2 weeks to 6 months. (2) UL dysfunction as indicated by the Fugl-Meyer motor function score ≥20-40/66. (3) Aged 40–70 years, regardless of sex. (4) No severe cognitive or communication impairment as indicated by the Mini-mental state examination (MMSE) ≥ 24 points.

### Exclusion criteria

Exclusion criteria are as follows: (1) Patients with severe systemic diseases such as cardiovascular or pulmonary diseases who cannot tolerate rehabilitation treatment. (2) Patients diagnosed with mental illness such as severe depression, etc. (3) In addition to stroke, suffering from other neurological diseases such as Parkinson's disease and epilepsy, etc. (4) According to the safety guidelines, there are contraindications for TMS, such as metal foreign bodies or other electronic devices implanted in the body, etc. (5) Application of drugs that change the excitability of the cerebral cortex. (6) Patients with unstable or larger carotid plaques. (7) Patients with severe osteoporosis.

### Sample size calculation

The main purpose of the experiment is to compare whether the curative effect of the experimental group is better than that of the control group. The main evaluation index of curative effect will be the change of upper limb Fugl-Meyer scale. The calculation of the sample size will be based on data from previous research and our previous experiment (18). As the study involves two groups, the sample size calculation formula for a two-sample mean comparison is as follows:

(1)
$$\begin{array}{l} n_{c}=\frac{{\left(z_{1-\alpha }+z_{1-\beta }\right)}^{2}\sigma^{2}\left(1+\frac{1}{K}\right)}{{\left(\mu_{T}-\mu_{C}-\Delta \right)}^{2}} \end{array}$$

where, Z_1_-α = 1.960, Z_1_-β = 0.842, σ = 2.0 (standard deviation), K = 1(ratio of participants in the experimental and control groups), 1 = 3 (optimality bounds), α = 0.025 (2.5% one-tailed significance level), and β = 0.20 (80% power), μ_T_ = 6.6 (predicted mean in experimental group); μ_C_ = 2.3 (predicted mean in control group). The calculated required sample size is 38 participants for each group. Assuming the dropout rate is 20%, 45 participants per group (total of 90 participants) need to be recruited.

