#### Efficacy analysis

The data in accordance with normal distribution and homogeneity of variance in the main and secondary indicators will be compared with *t*-test to see if the difference between the two groups before and after treatment is statistically significant. The rank data with non-normal distribution or uneven variance will be analyzed by Wilcoxon rank sum test.

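### The sample size is calculated for superiority by a 3-point bound, but the efficacy section describes an ordinary test of difference that does not mention the bound

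*Protocol article*

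**What the plan says.** The Sample size calculation section gives the trial's purpose as to "compare whether the curative effect of the experimental group is better than that of the control group" and names the endpoint: "The main evaluation index of curative effect will be the change of upper limb Fugl-Meyer scale". Its formula has the squared term (μT − μC − Δ)² in the denominator. The inputs include "σ = 2.0 (standard deviation"), predicted mean changes of 6.6 and 2.3, 1:1 allocation, and "1 = 3 (optimality bounds), α = 0.025 (2.5% one-tailed significance level), and β = 0.20 (80% power"). The printed 1 is read here as Δ, since the formula contains Δ and no other listed input supplies it. It is treated as a typesetting or extraction artefact, not as an error. The section arrives at 38 per group, raised to 45 per group (90 in total) for 20% dropout.

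The Efficacy analysis section, under the heading Statistical analysis plan, applies a t-test to normally distributed data with equal variances, "to see if the difference between the two groups before and after treatment is statistically significant". Otherwise it applies a Wilcoxon rank sum test. It gives no null value other than no difference, no confidence limit to be compared with 3, and no reference to the bound. The bound appears nowhere else in the article.

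**The concern.** A sample-size formula with a non-zero bound powers one specific hypothesis: here, H0 that the experimental-minus-control difference in mean change is at most 3 points, against the alternative that it is more than 3. An unqualified two-sample t-test or rank sum test addresses a different null, that there is no difference. The stated power and the described test therefore belong to different hypotheses.

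What is at stake is how a positive result would be read. An observed difference well under 3 points could be statistically significant in a trial whose published sizing rests on exceeding 3 points. If the choice between exceeding zero and exceeding 3 is still open when the results are known, it could follow the results.

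**Working it through.** **Inputs, all from the Sample size calculation section.** z(1−α) = 1.960, z(1−β) = 0.842, σ = 2.0, K = 1, μT = 6.6, μC = 2.3, Δ = 3. The expected difference is 6.6 − 2.3 = 4.3, and the difference less the bound is 4.3 − 3 = 1.3.

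**Step 1: reproduce the stated figure.**

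n = (1.960 + 0.842)² × 2.0² × (1 + 1/1) / 1.3² = 7.851 × 4 × 2 / 1.69 = 62.81 / 1.69 = 37.17, rounded up to **38 per group**. This matches the plan.

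**Step 2: the same formula with a bound of 0.**

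n = 62.81 / 4.3² = 62.81 / 18.49 = 3.40, rounded up to **4 per group** (5 if the t distribution is used in place of the normal). The figure of 38 therefore depends on the bound.

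**Step 3: evaluable numbers and standard error.** Taking 20% dropout from 45 leaves 45 × 0.80 = 36 per group. SE = 2.0 × √(2/36) = 0.471, and t(0.975, 70 df) = 1.994.

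**Step 4: smallest observed difference that is significant (36 per group, SD 2.0).**
- Against zero: 1.994 × 0.471 = **0.94 points**.
- Against the bound: 3 + 0.94 = **3.94 points**.

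**Step 5: power at the planned difference of 4.3 (SD 2.0).**
- Against zero: above 99.9% at 36, 38 or 45 per group.
- Against the bound (normal approximation): 78.7% at 36, 80.9% at 38, 86.9% at 45 per group.

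The stated 80% describes the second test and not the first.

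**Step 6: chance of significance against zero when the true difference lies below the bound (36 per group, SD 2.0, t-based).** At a true 1.5 points it is about 88%, and at 2.0 points about 98.7%. At 2.0 points, the test against the bound would succeed with probability of about 0.002% (normal approximation).

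**Step 7: sensitivity to the SD.** The SD of 2.0 is the plan's figure. SDs of 4 and 6 are assumed here only to show the range, again with 36 per group.

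| SD | Smallest significant difference against zero | Power against zero at a true 1.5 points |
|---|---|---|
| 2.0 (plan) | 0.94 | 88% |
| 4 (assumed) | 1.88 | 35% |
| 6 (assumed) | 2.82 | 18% |

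**The case against.** The strongest reply is that the worded aim has no margin. The Sample size calculation section asks only whether the experimental group is better, and the Background hypothesis says only that the treatment can promote improvement. A zero-null test answers that question. It carries no type I error inflation, and on the plan's inputs it has far more power than it needs. All of this stands. A reader might infer that the trial would declare a false success, or that it has promised to show superiority by 3 points. The documents support neither: the bound appears once, as a formula input, and is never called a success criterion.

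A second reply is that the efficacy section writes out no null value, that a t-test can be run against a shifted null, and that a separate analysis plan may say so. This has limited force. The article names the efficacy test under its own Statistical analysis plan heading, and an unqualified t-test for significance ordinarily means a null of no difference. The point concerns two stated sections that do not fit together, not detail left for another document.

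A third reply is that the illustrations depend on SD 2.0 and 36 evaluable per group. That is right: a larger SD changes them considerably, and the planned ITT analysis with LOCF could keep up to 45 per group. The mismatch itself depends on neither figure.

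**Conclusion.** The sample-size hypothesis and the described efficacy test do not match. On the plan's inputs, 38 per group and 80% power hold only for a one-sided test against 3 points. The test against zero would need about 4 per group and has power above 99.9% at 4.3 points. Conditional on SD 2.0 and 36 evaluable per group, the two thresholds for significance are about 0.94 and 3.94 observed points.

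The consequence is for interpretation and for the justification of 90 patients. It is not a shortage of patients or an invalid test. A significant result from the described test would support a claim of being better than control, but not one of being better by more than 3 points. Severity: should-fix.

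**What to change.** Reconcile the Sample size calculation and Efficacy analysis sections before the data are unblinded. Either route resolves the mismatch.

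**(a) Keep the bound.** State in the Efficacy analysis section that superiority by the planned bound is claimed only if the lower limit of the two-sided 95% CI for the difference in mean Fugl-Meyer change exceeds 3. Give a shifted-null version for use if the Wilcoxon test applies. Report a CI above 0 but not above 3 as a difference that did not meet the planned bound. The 38 per group then stands. The cost is a stricter criterion than the worded aim, introduced in a trial that the Abstract says began recruiting in February 2022. That makes it a documented change to the success rule, not mere rewording.

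**(b) Test against zero.** State that the primary test is against no difference, remove the bound from the Sample size calculation section, and restate the power of the planned 90 patients for that test. Because the present inputs would then call for only about 4 per group, give the actual basis for the sample size as well. The cost is a rewritten sample-size paragraph, and a significant result could not be presented as superiority by more than 3 points.

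### Recruiting 45 per group does not retain the required 38 per group at the stated 20% dropout; the effect on power is small

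*Protocol article*

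**What the plan says.** The protocol article, under Sample size calculation, uses a two-sample comparison of means with a margin. It lists "α = 0.025 (2.5% one-tailed significance level"), "β = 0.20 (80% power"), "σ = 2.0 (standard deviation"), "K = 1(ratio of participants in the experimental and control groups"), "μ_T_ = 6.6 (predicted mean in experimental group"), a predicted control mean of 2.3, and a margin printed as "1 = 3 (optimality bounds"). From these it concludes: "The calculated required sample size is 38 participants for each group". The next sentence makes the allowance for losses: "Assuming the dropout rate is 20%, 45 participants per group (total of 90 participants) need to be recruited".

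The total of ninety recurs in the Abstract, in Methods/design and in Randomization and blinding, where ninety random numbers are to be generated. Under Data set population determination, the protocol plans both an intention-to-treat and a per-protocol analysis, with LOCF for missing data.

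**The concern.** A dropout allowance should leave the required number once the assumed share has been lost. Here the required number (38), the assumed loss (20%) and the recruitment target (45) are stated one after another, and they cannot all hold. A reader will take 90 as a total that protects 80% power against 20% dropout. It offers that protection only against a lower dropout rate. What is at stake is the accuracy of the trial's main planning figure, and a small amount of power in any analysis restricted to patients with observed outcomes.

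**Working it through.** All inputs come from Sample size calculation: z = 1.960 (one-sided 0.025), z = 0.842 (80% power), SD 2.0, allocation ratio K = 1, predicted means 6.6 and 2.3, margin 3. The printed 1 = 3 is read as the formula's Δ = 3, because that value gives 38; with no margin the formula gives 4 per group.

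**1. Reproduce the required number.**
- Margin-adjusted difference: 6.6 − 2.3 − 3 = 1.3.
- n = (1.960 + 0.842)² × 2.0² × (1 + 1/1) / 1.3² = 7.851 × 8 / 1.69 = 37.17, rounded up to 38.
- The stated 38 is reproduced.

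**2. Apply the stated dropout.**
- Recruits needed per group: 38 / (1 − 0.20) = 47.5, so 48 per group and 96 in total.
- Left from 45 at 20% loss: 45 × 0.80 = 36, which is 2 short of 38.
- Largest loss that still leaves 38 of 45: 7/45 = 15.56%. Rounded down so that 38 are kept, this is about 15.5% (45 × 0.845 = 38.0).

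**3. Where 45 might come from.** Multiplying by 1.2 instead of dividing by 0.8 gives 38 × 1.2 = 45.6, which becomes 45 only if rounded down. From the unrounded value, 37.17 × 1.2 = 44.6, which rounds up to 45. The document does not show which route was taken, if either.

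**4. Power at each size, by the protocol's normal formula.** Power = Φ(1.3 / (2.0 × √(2/n)) − 1.960).
- n = 36: Φ(2.758 − 1.960) = 78.7%
- n = 38: Φ(2.833 − 1.960) = 80.9%
- n = 45: Φ(3.083 − 1.960) = 86.9%
- n = 48: Φ(3.184 − 1.960) = 89.0%

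The shortfall at 36 against the stated 80% is 1.3 percentage points. On the noncentral t distribution, 36 per group gives 77.6% and 38 gives 79.9%.

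**The case against.** The strongest reply is that almost nothing is lost. Four arguments support it.

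- **Size of the loss.** On the protocol's own formula, 36 per group still gives 78.7%. The lower t-based figure of 77.6% is not a fair measure of the dropout error alone, since on that basis even the intended 38 gives 79.9%. This stands.
- **Analysis set.** The protocol plans an intention-to-treat analysis with LOCF alongside the per-protocol one. If LOCF keeps all 45 per group, nominal power is 86.9% under the same means and SD. This stands as a limit on the power figure, though not as reassurance. Carrying early values forward can change both the mean difference and the SD, so 86.9% is not assured either.
- **The test.** The 78.7% is power to show a difference beyond the 3-point bound. The Efficacy analysis section describes a t-test for a difference between groups and mentions no margin. For a plain comparison with the assumed difference of 4.3 and SD 2.0, 36 per group gives 4.3 / (2.0 × √(2/36)) = 9.1 standard errors, and power is essentially 100%. This also stands as a condition on the power figure.
- **Consistency.** Ninety is used throughout the article. This is true, but a total repeated consistently can still fail to follow from its inputs.

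None of these arguments makes 38, 20% and 45 compatible. The sample size section makes its own allowance for dropout, so its evident aim is to have 38 left per group after losses.

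**Conclusion.** The recruitment figure is wrong as written. From 38 evaluable per group and 20% dropout, 48 per group (96 in total) follows; 45 per group leaves 36. This rests only on figures printed in one section of the article and needs no outside assumption.

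The effect on power is small: 78.7% against a stated 80%. That comparison assumes the protocol's means, SD and 3-point bound, one-sided 0.025, the normal formula, and an analysis of completers or the per-protocol set with 20% lost in each group.

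Two stronger readings are tempting, and the document supports neither. A reader might infer that the trial as a whole fails to reach its planned power. The shortfall is 1.3 points, depends on the analysis set and on testing against the bound, and need not arise in the intention-to-treat set with LOCF. A reader might also infer that a particular slip produced the 45. At least two routes lead there, and the article shows neither. Severity is minor.

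**What to change.** Keep 90 patients and replace the dropout sentence in Sample size calculation with wording to this effect: *With 45 patients recruited per group (90 in total), the required 38 evaluable per group are retained at up to about 15.5% dropout. At 20% dropout, 36 per group remain, and power by formula (1) for an analysis of completers against the 3-point bound is about 79%.*

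The conditions on the power figure (completers, normal formula, 3-point bound) should stay in the sentence, because without them the number would mislead. The cost is one restated sentence and a slightly less favourable planning statement. Recruitment, randomization list and analysis are unchanged. Holding to 20% dropout with 38 evaluable would instead mean 48 per group, 6 more patients in total, and changing ninety wherever it appears. The small loss of power does not call for that.
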